### 2.3 Randomization and masking

After giving consent, eligible children will be randomized by an interactive web response system (IWRS) at a 3:1 ratio into the remimazolam group (Group R) or propofol group (Group P). Randomization will be stratified by centers to limit baseline imbalance between treatment groups. All study drugs will be prepared by a designated researcher with a stock solution of propofol (10 mg/mL, Fresenius Kabi Austria GmbH, Graz, Austria) and remimazolam tosylate (36mg, Jiangsu Hengrui Pharma Corporation, China) dissolved in sterile saline solution 0.9% to a concentration of 1 mg/mL. In consideration of the obvious difference in drug color and dose adjustments, only the participants will be blinded to the treatments throughout the study. Trained outcome evaluators blinded to group allocation will be assigned to assess the prescribed endpoints after the operation.

### 2.4 Study procedures

#### 2.4.1 Pre-anesthesia visit

During the routine preoperative anesthesia visit, an anesthetist will collect demographic data, vital signs, medical history, concomitant medication and preoperative laboratory tests (complete blood count, coagulation and serum biochemical), and carry out a physical examination for each child. Their parents or legally authorized representatives will give their informed consent after being advised on the purpose of the study, associated risks and benefits.

#### 2.4.2 Induction of general anesthesia

Children’s preoperative fasting status will be confirmed to comply with an international multidisciplinary consensus statement on fasting before procedural (Green et al., 2020). No children will receive any preoperative medication. The baseline vital signs and the level of alertness will be recorded in a quiet area accompanied by their parents or legally authorized representatives before arrival at the operating room; the vital signs at the pre-anesthesia visit will be considered as baseline for children who could not cooperate. We will use the Modified Observer’s Assessment of Alertness/Sedation scale (MOAA/S) (Klockars et al., 2006; Jung et al., 2019) (Supplementary Table S1)—a valid tool in the measurement of sedation levels for children by observing their response to various stimuli to evaluate the subject’s level of sedation. We will consider a MOAAS score ≤1 as the sign of loss of consciousness (LoC). In the specific assessment procedure, we will start intermittent gentle shoulder shaking immediately after the loss of the eyelash reflex, and no response will indicate LoC.

Before anesthesia induction, peripheral venous access will be established and the following vital signs will be monitored throughout the study: continuous electrocardiogram (ECG), heart rate (HR), respiratory rate (RR), pulse oxygen saturation (SpO_2_), and non-invasive blood pressure (NIBP) which will be adjusted by measuring at 1-min intervals until achieving endotracheal intubation and every 5min thereafter. The Bispectral Index (BIS, Aspect Medical Systems-Covidien) pediatric sensor strip will be applied on the forehead of every child, and the BIS value will be recorded before the dose, at LoC, after tracheal intubation and thereafter at 5-min intervals. Subsequently, all pediatric patients will be pre-oxygenated for several minutes in 100% oxygen at a flow rate of 3 L/min followed by a single dose of fentanyl 3 μg/kg (Yichang Humanwell Pharmaceutical, China) intravenously. About 3 min later, all pediatric patients will randomly receive an initial intravenous dose of remimazolam 0.3 mg/kg in Group R or propofol 2.5 mg/kg in Group P for the induction of anesthesia, the injection time ≤60s. The investigator will administer an additional intravenous dose of remimazolam 0.1 mg/kg in Group R or propofol 1.0 mg/kg in Group P under such condition that the child will not achieve the loss of consciousness (LoC: MOAA/S score ≤1) within 60s, the injection time ≤30s. In both groups, the additional dose will be limited to single-use only. If LoC still does not occur within 1 min after the additional dose, propofol 1.0 mg/kg as the remedial sedative drug will be administered repeatedly by intravenous injection until MOAA/S score ≤1, in which general anesthesia will be maintained using isoflurane inhalation instead of propofol or remimazolam.

After reaching LoC without the use of the remedial sedative drug, the researcher will immediately begin taking an intravenous infusion of remimazolam at an initial rate of 2 mg/kg/h in Group R or propofol at an initial rate of 8 mg/kg/h in Group P and remifentanil (Yichang Humanwell Pharmaceutical, China) at an initiation rate of 0.25 μg/kg/min in both groups, while administering cis-atracurium 0.2 mg/kg intravenously. Tracheal intubation will be facilitated to provide assisted ventilation after approximately 3 min.

#### 2.4.3 Maintenance of general anesthesia

After tracheal intubation is completed, parameters of mechanical ventilation using volume-controlled or pressure-controlled ventilation mode with 50% oxygen/air mixture will be set according to age and ideal body weight to maintain PetCO2 between 35 and 45 mmHg. Anesthesia will be maintained with a constant infusion rate of remimazolam 1–3 mg/kg/h in Group R or propofol 4–12 mg/kg/h in Group P, and remifentanil 0.1–0.5 μg/kg/min in both groups.

The infusion rate of drugs will be adjusted within the prescribed maintenance dose range in the context of the changing intensity of surgical stimuli as primary guidance and the BIS value as secondary guidance to maintain an appropriate depth of anesthesia. Remedial sedative and/or analgesic drugs will be given to children suffering from an inadequate depth of anesthesia defined as the appearance of at least one of the following signs: patient movement, sweating, tears, hypertension and tachycardia (systolic blood pressure (SBP) and HR exceeding 25% of the baseline value for more than 5min), or clear and substantial elevations in SBP or HR, followed by discontinuing the investigational drugs and switching to continuous inhalation of isoflurane. The choice of remedial sedative and/or analgesic medications and dosage will be determined by the investigator. If hemodynamic instability persists in either group, additional vasoactive agents (e.g., esmolol or urapidil) will be administered at the investigator’s discretion. In both groups hypotension (SBP <70 mmHg + (2 x age in years) for a further 5 min) and bradycardia (HR < 70 bpm for a further 5 min) will be treated with ephedrine/phenylephrine and atropine, respectively, and the investigator will decide whether to discontinue the study drugs If necessary.

Fentanyl 1 μg/kg as an additional dose will be given as needed each time intravenously prior to the anticipated appearance of the significantly larger intensity of surgical stimuli during surgery, and the total intraoperative additional fentanyl dose will be limited to a maximum of 5 ug/kg. Intraoperative muscle relaxation will be given as needed by administration of additional doses of cis-atracurium 0.05 mg/kg each time, aiming to serve surgical needs or maintain effective mechanical ventilation, and no additional muscle relaxants will be administered within approximately 30 min prior to termination of surgery. Ketorolac tromethamine 0.5 mg/kg will be administered intravenously in a usual manner approximately 30 min before termination of surgery, and local infiltration anesthesia, nerve block or sacral anesthesia will be implemented if clinically indicated after surgery for postoperative analgesia. The type, concentration, and dose of local anesthetic will be at the discretion of the investigator. Residual muscle relaxation will be antagonized as required with neostigmine 0.03 mg/kg and atropine 0.015 mg/kg at the end of surgery.

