### 2.5 Outcomes

The primary endpoint will be the incidence of the successful induction and maintenance of anesthesia. Successful anesthesia induction will be defined as LoC being reached without the use of remedial sedative drugs during the induction period. Successful anesthesia maintenance will be defined as neither need for rescue sedative medication nor discontinuity of investigational drugs during the maintenance period.

The secondary endpoints will include 1) time to LoC: the time interval from an initial dose of investigational drugs to the first MOAA/S score ≤1; 2) usage of additional sedative drugs during the induction period; 3) the BIS value before dose, at LoC, after tracheal intubation and during the maintenance of anesthesia (LoC to end of the investigational drugs); 4) awakening time: the time interval from the end of investigational drugs to the first of 3 consecutive MOAA/S scores of 5; 5) extubation time: the time interval from discontinuation of investigational drugs to extubation; 6) the incidence of ED, moderate and severe pain (FLACC scale >3) in PACU; 7) usage of remedial drugs in PACU; 8) PACU discharge time: the time interval from the end of investigational drugs to the first of 2 consecutive modified Aldrete score ≥9; 9) parental and anesthesiologists satisfaction; and 10) the incidence of negative behavior change at day 3 after surgery.

Safety endpoints will include frequency, causality, and severity of adverse events (AEs) in each treatment arm. Grading of AEs will be according to Common Terminology for Adverse Event (CTCAE), Version 5.0 criteria. Injection site pain, fluctuations in blood pressure or heart rate, and the use of vasoactive agents will be recorded. Postoperative nausea and vomiting (PONV), delayed awakening from anesthesia, and respiratory depression will also be collected.

Detailed information about surgery will be collected: name of surgery, length of surgery, intraoperative bleed loss, the total maintenance dose of study drugs (remimazolam or propofol) and remifentanil, total cumulative additional consumption, frequency of fentanyl and cis-atracurium, and usage of perioperative concomitant medication.

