We will make continual adjustments to the infusion rate of investigational drugs in the context of the changing intensity of surgical stimuli as primary guidance and the BIS value as secondary guidance to maintain an optimum depth of anesthesia. Drawing on the “pressure, rate, sweating and tears” (PRST) scoring system (Russell, 1993), light anesthesia is defined as the occurrence of at least one of the following signs: patient movement, sweating, tears, hypertension and tachycardia (SBP and HR exceeding 25% (Lei et al., 2017) of the baseline value for more than 5min), or clear and substantial elevations in SBP or HR. Hypotension is SBP <70 mmHg + (2 x age in years) for a further 5 min. This is in accordance with previously described guidelines for hypotension by the Pediatric Advanced Life Support Provider Manual (Haque and Zaritsky, 2007). Bradycardia is usually defined as a heart rate below the lowest normal value for age. Thus, we define bradycardia as HR < 70 bpm for a further 5 min in children aged 3–6 years with reference to normal values for age (Baruteau et al., 2016). As everyone knows, the vagal excitatory reflex and harm may be magnified at the transient and extreme surgical stimuli. Consequently, it is the few minutes of SBP and HR fluctuations that matter. We then define hypertension, tachycardia, hypotension and bradycardia sustained for at least 5 cumulative minutes. It is worth noting that the appearance of clear and substantial elevations in SBP or HR must be immediately adjusted and processed by using remedial drugs.

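### One of the two SBP/HR signs that lead to primary failure has no stated size or duration and is judged by an unmasked operating-room team

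*Protocol article*

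**What the plan says.** Section 2.5 counts maintenance as successful when there is "neither need for rescue sedative medication nor discontinuity of investigational drugs during the maintenance period".

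Section 2.4.3 sets what leads there. At least one of several signs is enough: movement, sweating, tears, or one of two SBP/HR signs.
- The numeric sign names SBP together with "HR exceeding 25% of the baseline value for more than 5min".
- The acute-rise sign is "or clear and substantial elevations in SBP or HR, followed by discontinuing the investigational drugs and switching to continuous inhalation of isoflurane".

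The same section also allows infusion rates to be changed within the permitted range, guided first by surgical stimulus and second by BIS. A child managed that way remains a success.

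The Discussion returns to both signs. On duration it says "We then define hypertension, tachycardia, hypotension and bradycardia sustained for at least 5 cumulative minutes". On the acute rise it says "the appearance of clear and substantial elevations in SBP or HR must be immediately adjusted and processed by using remedial drugs", again without a number.

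On masking, Section 2.3 says "only the participants will be blinded to the treatments throughout the study" and "Trained outcome evaluators blinded to group allocation will be assigned to assess the prescribed endpoints after the operation". Section 2.4.2 schedules non-invasive blood pressure by "measuring at 1-min intervals until achieving endotracheal intubation and every 5min thereafter".

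**The concern.** Once a sign of inadequate depth is declared, the child is a primary failure, because study drug is stopped whichever remedial drug is chosen. For a rise in SBP or HR, the plan does not fix when the sign is present. The acute-rise sign is joined to the numeric one by an 'or', needs one variable instead of two, and has no minimum size or time. It can therefore be declared at any point before the 25% sign is met, and nothing written separates a rise that leads to remedial drug from one that is titrated away.

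The people making that call know the treatment. Failures are expected to be few, so a small difference between arms in how readily the sign is called could move the result. Slower calling in Group R, or quicker calling in Group P, favors a false non-inferiority finding. The reverse costs power.

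**Working it through.** **Is the sign left open?** The texts side by side:

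| | 25% sign | Acute-rise sign |
|---|---|---|
| Variables | SBP and HR, as worded | SBP or HR |
| Size | more than 25% above baseline | none |
| Duration, Section 2.4.3 | more than 5 min | none |
| Duration, Discussion | at least 5 cumulative min | none (treat at once) |
| Consequence | remedial drug, study drug stopped | the same |

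The Discussion gives reasons or sources for the 25%, hypotension and bradycardia limits, then repeats the acute-rise sign without one. The gap is therefore not a detail lost in condensing the protocol.

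**Duration against the measurement schedule.** With scheduled blood pressure at 0, 5 and 10 min, two readings span exactly 5 min. That meets at least 5 min but not more than 5 min, which on scheduled SBP readings needs a third. HR is monitored continuously, so this affects SBP only.

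**The plan's own sample size (Section 2.6).** Inputs: success 98% in both arms, margin 8 points, one-sided alpha 0.025, power 90%, ratio 3:1.

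n(P) = (4/3) × 0.98 × 0.02 × (1.960 + 1.282)² / 0.08² = 42.9, or 171.6 in total unrounded. The plan states 171, so it reproduces. Dividing by 0.9 gives 190 (from 171) or 192 (from 172 with whole arms). The plan's 144 + 48 = 192 follows and is not in dispute.

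**How few events decide the result.** Expected failures at 98%: 0.02 × 144 = 2.9 in Group R and 0.02 × 48 = 1.0 in Group P. Take 1 failure in Group P and use Wald limits:
- 6 failures in R: difference −6/144 + 1/48 = −0.0208; SE = √(0.0417 × 0.9583/144 + 0.0208 × 0.9792/48) = 0.0265; lower limit −7.3%, pass.
- 7 failures in R: difference −0.0278; SE 0.0273; lower limit −8.1%, fail.

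Miettinen-Nurminen splits at the same place. Newcombe passes at 7 (−7.9%) and fails at 8 (−8.8%). Near the boundary, one call decides.

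**What a shift in calling would do.** The probability of claiming non-inferiority is the exact binomial sum over all outcomes at 144/48 in which the lower limit of the two-sided 95% interval exceeds −8%. The protocol does not name the interval method, so three are shown. The shifts are assumptions: the documents give no frequency of borderline rises.

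| Recorded success R / P | Meaning | Miettinen-Nurminen | Newcombe | Wald |
|---|---|---|---|---|
| 90 / 98 | true rates at the margin, no shift | 2.5% | 2.9% | 1.7% |
| 91 / 98 | R under-called by 1 point (1.4 children) | 4.9% | 5.9% | 3.8% |
| 92 / 98 | R under-called by 2 points (2.9 children) | 9.2% | 11.1% | 8.0% |
| 90 / 96 | P over-called by 2 points (1.0 child) | 8.9% | 9.3% | 5.1% |
| 98 / 98 | true equality, no shift (power) | 96.3% | 97.0% | 97.9% |
| 96 / 98 | true equality, R over-called by 2 points (power) | 64.8% | 69.8% | 69.1% |

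**Scale of the shifts.** At 90% true success Group R has 0.10 × 144 = 14.4 failures. One point (1.44 children) is 10% of all of them and two points is 20%, in one arm only. That pool includes induction failures, which follow a timed MOAA/S rule, and failures from other signs. The 1-point row is the modest case.

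**The case against.** The strongest reply is that this clause is a treatment trigger and not the endpoint. Section 2.5 counts concrete events (rescue or discontinuation), and an anesthetist must be free to treat a sharp rise without waiting 5 minutes. Open conduct is justified in Section 2.3 by drug color and dose adjustment. Movement, sweating and tears are also ungraded, and stopping study drug for hypotension or bradycardia is left to the investigator, so one number would not remove judgment. All of this stands. It limits what the fix can achieve, but it does not explain why one SBP/HR sign has a limit and the other, with the same consequence, has none.

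The size of the effect is also open to challenge. The documents do not say how often the acute-rise sign would be called, and shifts of 2 points or more require a large share of one arm's failures to be miscalled. That stands too, so the table is an illustration and not an estimate.

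A reader might go further and infer three things that the documents do not support:
- That the acute-rise sign will usually decide before the numeric one. No frequency is given, HR is watched continuously, and an extra blood pressure reading is not ruled out.
- That no call could be checked later. SBP and HR are monitored throughout surgery, so if the values are kept, calls can be compared with a numeric limit once one exists.
- That the gap favors remimazolam. Nothing shows a direction.

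It is also tempting to count every recorded excursion as a primary failure, treated or not. That would redefine the endpoint during recruitment, mix hemodynamic profile with adequacy of anesthesia, and undo the 98% assumption. By the same exact calculation, power would be 78-82% if success in both arms fell to 96%, and 55-66% at 94%.

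**Conclusion.** The concern holds in a limited form. A sign that leads directly to primary failure is stated twice without size or duration, overrides the numeric sign beside it, and is judged by a team of whom none is masked. The duration of the numeric sign is also worded in two ways. The limit has to be set in advance, because analysts cannot choose one sensibly after the outcomes are known.

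The consequence cannot be estimated from the documents. If true rates are 90% and 98%, all 144/48 children are analyzed, and Group R alone is under-called by 1 point, the false non-inferiority risk about doubles, to 3.8-5.9%. The protocol's sample size and open-label conduct are not faulted. The priority lies between worth considering and advisable: the change is cheap, but the harm is possible and not demonstrated.

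**What to change.** 1. In Section 2.4.3 and the Discussion, replace the acute-rise phrase by a numeric limit: SBP or HR more than X% above baseline, confirmed by a repeat reading within 1 min. The clinical team sets X, above 25%, without sight of outcomes by arm.
2. In both places, word the 25% sign as met at two consecutive 5-min readings.
3. Leave the primary endpoint in Section 2.5 unchanged. Add a supporting analysis covering both arms, in which a program, or a person masked to arm, applies the two numeric signs to the recorded SBP and HR. Hemodynamic failures that met neither sign, and untreated children who met one, are reclassified. Report whether the non-inferiority conclusion holds.

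The investigator may still treat any child at any time, and such a child is classified under Section 2.5 as now.

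The cost is one amendment while the trial is recruiting, an occasional extra blood pressure reading and one extra analysis. Children treated before the amendment are classified from their recorded values, assuming these are kept.

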#### 2.4.4 Recovery from general anesthesia

All the drugs will be discontinued at the end of the surgery. A child who has regular spontaneous breathing and recovery of airway reflexes will be extubated and transferred to the post-anesthesia care unit (PACU) for continuing regular anesthesia monitoring, where an attending anesthesiologist who will be unaware of trial grouping will assess the level of sedation, ED, and pain.

After removal of the investigational drugs, MOAA/S scores will be assessed every 5 min for at least 40 min until 3 consecutive MOAA/S scores of 5. In group R, as long as no arousal occurs after 1 h from the end of remimazolam administration, 0.2 mg flumazenil will be given and a dose of 0.1 mg will be repeated as needed. ED and pain in PACU individually will be evaluated using the Pediatric Anesthesia Emergence Delirium (PAED) scale (Sikich and Lerman, 2004) (Supplementary Table S2)—a reliable tool in the diagnosis of ED and the face, legs, activity, cry and consolability (FLACC) scale (Crellin et al., 2018) (Supplementary Table S3)—a validated pain measurement tool for children aged 2 months to 7 years. Both scales will be recorded every 5 min for at least 30 min after the arrival of PACU. PAED scores ≥10 will be considered a diagnosis of ED and PAED scores ≥15 will be defined as a severe ED. A child considered to have developed delirium or moderate and severe pain (FLACC scale >3) will be treated with remedial sedatives and/or analgesic drugs (e.g., propofol or fentanyl) at the attending anesthesiologist’s discretion. The modified Aldrete score will be recorded every 3 min after 3 consecutive MOAA/S scores of 5, and the child will be admitted to discharge from the PACU until 2 consecutive modified Aldrete scores ≥9.

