Remimazolam, a novel ultra-short-acting benzodiazepine, is currently approved as an intravenous agent in multiple countries for use in general anesthesia, procedural sedation, and longer-term sedation in adults, including intensive care (Keam, 2020). It has a high specificity and affinity for the brain benzodiazepine site on the gamma-aminobutyric acid type A (GABAA) receptor to potentiate the action of the inhibitory neurotransmitter without appreciable affinity for any of the other receptor sites (Kilpatrick et al., 2007; Keam, 2020). In contrast to midazolam, remimazolam as a typical ‘soft drug’ (Buchwald, 2020) has the same ester linkage as remifentanil, which leads to rapid biotransformation in the body by widespread tissue esterases to a pharmacologically inactive carboxylic acid metabolite (CNS7054) (Kilpatrick et al., 2007). As a result of its organ-independent metabolism profile, the pharmacokinetics of remimazolam are not subject to any stage of renal impairment, and mild or moderate hepatic impairment (Stöhr et al., 2021). Remimazolam was clinically demonstrated to produce high clearance (CL), faster onset and offset rates than midazolam, and predictable sedation effects over a wide dose range without significant cardiovascular or respiratory depression in two phases I studies (Antonik et al., 2012; Schüttler et al., 2020), in which volunteers received remimazolam as intravenous single ascending dose administration or constant intravenous infusion, respectively. Pharmacokinetic/pharmacodynamic modeling supports the observation of time-dependent change in remimazolam CL that is not related to cumulative remimazolam dose within 24 h of continuous dosing (Zhou et al., 2020). The sedative effect of remimazolam is completely antagonized by flumazenil as a benzodiazepine receptor antagonist (Chen et al., 2020b). These characteristics may reduce the risk of oversedation and rebound sedation under these circumstances of chronic infusions or higher doses in pediatric patients.

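### Flumazenil is given at 1 h in Group R only, yet awakening and PACU discharge times count antagonist-assisted recovery as remimazolam recovery

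*Protocol article*

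**What the plan says.** Section 2.4.4 (Recovery from general anesthesia) sets the reversal rule: "In group R, as long as no arousal occurs after 1 h from the end of remimazolam administration, 0.2 mg flumazenil will be given", with smaller repeat doses as needed. The rule is confined to Group R, and arousal is not defined. The same section sets the observation schedule: "MOAA/S scores will be assessed every 5 min for at least 40 min until 3 consecutive MOAA/S scores of 5".

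Section 2.5 (Outcomes) defines two recovery times without mentioning the antagonist: "awakening time: the time interval from the end of investigational drugs to the first of 3 consecutive MOAA/S scores of 5" and "PACU discharge time: the time interval from the end of investigational drugs to the first of 2 consecutive modified Aldrete score" of at least 9. Among safety items, "delayed awakening from anesthesia, and respiratory depression will also be collected", with no time threshold for delayed awakening.

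Flumazenil is named in no endpoint. Section 2.5 lists "usage of remedial drugs in PACU", but the only use of that term for PACU, in section 2.4.4, concerns children with delirium or pain, who "will be treated with remedial sedatives and/or analgesic drugs (e.g., propofol or fentanyl) at the attending anesthesiologist’s discretion". Section 2.5 does collect perioperative concomitant medication, so flumazenil use can be recovered from the data.

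**The concern.** The antagonist is triggered by the outcome being measured (failure to wake), and in one arm only. The Introduction describes its effect on remimazolam sedation as complete. A Group R child who would have slept well past 1 h may thus be recorded as awake soon after 1 h, while a Group P child in the same state keeps the full duration. The written definitions treat the two times as like for like.

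At stake are secondary and safety results. The Introduction and Discussion present fast offset and suitability for day surgery as advantages of remimazolam. If the longest Group R times reflect reversal, a comparison of mean recovery times is tilted toward remimazolam. So is a delayed-awakening comparison, if its threshold is later set beyond 60 min.

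**Working it through.** **1. The plan's own figure.** Section 2.6 gives one-sided alpha 0.025, power 90%, margin 8 points, 98% success in both arms and 3:1 allocation. With unpooled variance the control group needs 0.98 × 0.02 × (1 + 1/3) × (1.960 + 1.282)² / 0.08² = 42.9, so the total is 4 × 42.9 = 171.6, against 171 stated. Then 171/0.9 = 190, and the next total that splits 3:1 is 192 (144 + 48). The figure reproduces. It concerns induction and maintenance only, so this point does not affect it.

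**2. Inputs for recovery times.** From the documents: 144 and 48 children, readings every 5 min, reversal at 60 min in Group R only, and Mann-Whitney with Hodges-Lehmann for non-normal times or a t-test otherwise (section 2.7). Assumed, because the documents give no awakening distribution: lognormal times, the same true distribution in both arms, and every Group R child not awake at 60 min waking at the 65-min reading.

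**3. Shift caused by reversal alone** (log-SD 0.5, 1,000 simulated trials per row; negative favours remimazolam).

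| Not awake at 60 min | Expected recipients among 144 | Shift in mean difference | Shift in Hodges-Lehmann | Past 65 min, R vs P |
|---|---|---|---|---|
| 1% | 1.4 | −0.1 min | 0.0 min | 0 vs 0.8% |
| 5% | 7.2 | −0.6 min | 0.0 min | 0 vs 3.4% |
| 10% | 14.4 | −1.5 min | −0.2 min | 0 vs 7.6% |
| 20% | 28.8 | −3.9 min | −1.0 min | 0 vs 15.7% |

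The difference in medians does not move. Nor does the share past 60 min: a reversed child is still recorded as later than 60 min.

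**4. Delayed awakening.** With 0 of 144 events in Group R, Fisher's test gives p = 0.062 for 2 of 48 in Group P and p = 0.015 for 3 of 48, so three Group P events suffice. If the count were taken just past the reversal time, the chance of three or more, using the Group P shares in the table, is 0.7%, 22%, 72% and 99%. These are the chances of a false advantage for remimazolam.

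**5. Type I error in a second set of distributions** (medians 30, 40, 40, 45 min; log-SD 0.4, 0.4, 0.6, 0.6; 1,000 trials each), with about 4%, 15%, 25% and 31% unaroused at 60 min:

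- Mann-Whitney on times as observed: 5%, 6%, 10%, 14%. A separate run gave 17% in the last setting.
- Fisher's test at a 60-min cut-off: 3% to 5% throughout. At an assumed 70-min cut-off: about 6%, 76%, 100%, 100%.
- Worst rank for reversed Group R children only: 9% and 16% in the last two settings, almost all against remimazolam.
- All times above 60 min tied in both arms: 4% to 6% throughout.

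**The case against.** The strongest reply has four parts.

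First, the large false-advantage rates need a cut-off beyond 60 min, and section 2.5 sets none; at 60 min Fisher's test behaves properly. This stands. It makes the safety bias conditional on a choice still open, and is a reason to fix the threshold now.

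Second, the mean would probably not be the planned comparison. With lognormal times, Shapiro-Wilk rejected normality in at least one arm in every simulated trial, which sends the data to the rank-based method, and that barely moves at plausible rates. This also stands, although the t-test branch remains in section 2.7.

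Third, since arousal is undefined, the trigger may be a lower bar than a MOAA/S score of 5. Fewer children would then be reversed than simulated, and the effects would be smaller. This stands too.

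Fourth, thresholds and the handling of post-antagonist times are often left to a full protocol or analysis plan, and comparing regimens as used, antagonist included, is defensible. This stands in part. An as-observed comparison may stay, but the article does state definitions that put antagonist-assisted times into it unmarked.

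A reader might also infer that rebound sedation after reversal is being missed and should be counted from the MOAA/S records. The documents do not support that count: scoring may end at the third consecutive 5, so later scores need not exist. Modified Aldrete scoring continues after that point, and adverse events are collected. The Introduction's remark, "These characteristics may reduce the risk of oversedation and rebound sedation", describes a possible benefit of the drug, not a hazard of this regimen.

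**Conclusion.** The point holds in a limited form. A one-arm, outcome-triggered antagonist combined with score-only definitions lets antagonist-assisted recovery count as remimazolam recovery, and any bias favours remimazolam. It acts on durations beyond 60 min, on mean times, and on any delayed-awakening cut-off later than 60 min.

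A reader might infer that prolonged sedation on remimazolam is concealed. It is not: sedation past 60 min is still recorded as such, delayed awakening is a collected safety item, and flumazenil use is recoverable from concomitant medication.

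The size depends on a rate the documents do not give. At 1% to 20% not awake at 1 h, the bias is 0.1 to 3.9 min in the mean and 0 to 1.0 min in the Hodges-Lehmann difference. The rank test's type I error is clearly inflated only at about 25% unaroused or more. All these figures assume lognormal times, equal true distributions, and prompt, lasting reversal of every child not awake at 60 min. The primary endpoint and sample size are unaffected.

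**What to change.** Leave the clinical rule as it is and change the endpoint rules.

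1. **Delayed awakening.** Define it identically in both arms at a threshold no later than 60 min after the end of study drug, from the MOAA/S series already collected, and count every flumazenil recipient as an event. Report flumazenil use as a named safety outcome.
2. **Awakening time.** Keep the as-observed analysis and add one that treats all times above 60 min as tied, or censors them at 60 min, in both arms. The rule triggers only after 1 h, so times up to 60 min are comparable. Do not give the worst rank to reversed Group R children alone: that would place them behind a Group P child who slept longer, and so reverse the bias.
3. **PACU discharge time.** Show the results with flumazenil recipients identified.

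The cost is a few sentences in the definitions and one extra analysis of recorded data, with no new visits or patients. The downside is that remimazolam's recovery figures may look slightly less favourable, and the added analysis does not use differences beyond 60 min.
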